**Methods/design:**

This is a two-armed cluster-randomized clinical trial, with randomization among OPs. Forty OPs in two big companies providing medical care for multiple companies will be randomized to either the intervention group, i.e. psychiatric consultation embedded in a training programme, or the control group, i.e. only training aimed at recognition and providing Care As Usual. 60 patients will be included who have been absent from work for 6–52 weeks and who, after screening and a MINI interview, are diagnosed with depressive disorder, anxiety disorder or somatoform disorder based on DSM-IV criteria. Baseline measurements and follow up measurements (at 3 months and 6 months) will be assessed with questionnaires and an interview. The primary outcome measure is level of general functioning according to the SF-20. Secondary measures are severity of the mental disorder according to the PHQ and the SCL-90, quality of life (EQ-D5), measures of Return To Work and cost-effectiveness of the treatment assessed with the TiC-P. Process measures will be adherence to the treatment plan and assessment of the treatment provided by the Psychiatric Consultant (PC) in both groups.

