### Recruitment of patients

The aim is to include employees who have been absent from work for a minimum of 6 weeks and a maximum of 52 weeks, do not plan to resume work within the coming 6 weeks, and have been screened on either the Patient Health Questionnaire (PHQ) or the Whitely Index.

All patients who visited an OP within the past 6 months will be selected from the medical files, and will receive a letter describing the purpose of the study, together with an informed consent form for the screening procedure and the baseline questionnaires. Patients visiting an OP during the inclusion period will also be invited to participate in the study. They will also receive the informed consent form, together with the baseline questionnaires.

Patients will be included if they reach a cut off score of >15 on the PHQ9[34] or > 3.5 on the Whitely Index[35] and have given informed consent for participation in the study. The Mini-International Neuropsychiatric Interview (MINI.)[36,37] will be administered for the classification of symptoms according to DSM-IV[38]. In the intervention group, the patients selected in this way will have a consultation with a psychiatrist in addition to the treatment provided by the OP; in the control group the patients receive CAU provided by their OP.

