#### 2. Secondary outcome measures

The severity of the symptoms will be measured with the PHQ[35] and the SCL-90[44]. Quality of life will be assessed with the EQ-5D[45,46] and the SF-20, both of which are validated tools for the assessment of general health-related quality of life.

In addition to the evaluation of improvement in general functioning, an attempt will also be made to assess the cost-utility of psychiatric consultation compared to CAU. Therefore, an estimate will be made of the direct medical costs and productivity costs. The necessary data collected by means of the Trimbos/*i*MTA questionnaire for Costs associated with Psychiatric Illness (TiC-P)[47,48].

Additional outcome measures will be the MVI-20, a questionnaire assessing fatigue[49] and the ALCOS-12 that assesses general competence, resilience and initiative in an employee[50].

Process measures will be satisfaction of the employee with the OP (VAS) and compliance with the advice given by the consultant psychiatrist.

Baseline measurements will take place before inclusion (T_0_), and follow up measurements will take place at 3 months with the TiC-P and EQ-5D (T_1_) and at 6 months (T_2_).

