### Analysis

Intention-to-treat analysis will be performed by means of MLA, with OPs in the primary hierarchical level. Subsequently, at the secondary hierarchical level, patient characteristics influencing the outcome will be analysed. If differences in outcome are found in MLA, the effect size will be estimated by Chi-square analysis and described in Cohen's d[54]. To control for possible skew ness in the randomized groups, as far as the distribution of confounders is concerned, propensity scores will be calculated[55]. Possible confounders, such as age, gender, history of mental disorder, history of treatment, fatigue, resilience, and satisfaction and compliance of the employee, will be entered as variables in the analysis.

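### The analysis enters satisfaction and compliance as confounders, although the protocol defines both as process measures that can follow from the intervention

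*Protocol article*

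**What the plan says.** The Analysis section of the protocol article opens with the main comparison: "Intention-to-treat analysis will be performed by means of MLA, with OPs in the primary hierarchical level". It then announces an analysis of patient characteristics that influence outcome, an effect-size calculation, and propensity scores to deal with imbalance between the randomised groups. The sentence straight after the propensity scores begins "Possible confounders, such as age, gender, history of mental disorder, history of treatment" and ends "fatigue, resilience, and satisfaction and compliance of the employee, will be entered as variables in the analysis". It names no separate model for these variables.

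Under Outcome parameters, 2. Secondary outcome measures, the same two variables have another role: "Process measures will be satisfaction of the employee with the OP (VAS) and compliance with the advice given by the consultant psychiatrist". Fatigue also appears there as an outcome: "Additional outcome measures will be the MVI-20, a questionnaire assessing fatigue". The ALCOS-12, which covers resilience, is listed beside it.

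Recruitment of patients states who meets the psychiatrist: "In the intervention group, the patients selected in this way will have a consultation with a psychiatrist in addition to the treatment provided by the" (the sentence then names the occupational physician). Controls have no such visit: "in the control group the patients receive CAU provided by their OP". The Abstract words the process measures differently: "Process measures will be adherence to the treatment plan and assessment of the treatment provided by the Psychiatric Consultant (PC) in both groups".

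**The concern.** A confounder in a randomised comparison is a prognostic factor, fixed before treatment, that happens to be unevenly spread over the arms. Compliance with a psychiatrist's advice cannot exist until the psychiatrist has given it. Satisfaction with an OP who coordinates care planned by the psychiatrist may itself be changed by that arrangement. Conditioning on such variables can remove part of the effect that runs through them. It can also bring in an association with unmeasured prognosis, for instance if patients who are going to recover are both more satisfied and better functioning.

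At stake is what the arm coefficient for the SF-20 means. The trial asks what offering psychiatric consultation does. A model holding satisfaction and compliance fixed answers a different question, and randomisation does not protect that answer.

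**Working it through.** The plan states no figure on this point, so the check has two parts: the definitions, and an illustration under assumed values.

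**1. Definitions side by side**

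| Variable | Role in Analysis | Role in Secondary outcome measures | Who can have it |
|---|---|---|---|
| Satisfaction | possible confounder | process measure, VAS about the OP; no time point given | both arms |
| Compliance | possible confounder | process measure, about the psychiatrist's advice | intervention arm only, by Recruitment of patients; the Abstract speaks of both groups |
| Fatigue, resilience | possible confounders | additional outcomes, with a T0 measurement available | both arms |

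Compliance as defined is therefore post-randomisation. If the Abstract is right and some form of adherence is recorded in both arms, it is still post-randomisation.

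**2. Satisfaction: bias if it is adjusted for**

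Let τ be the total effect on the SF-20 in SD units, a the shift in satisfaction caused by the arm (in within-arm SDs), and r the within-arm correlation of satisfaction with the SF-20, whether causal or through shared causes. In a linear model the adjusted arm coefficient is τ − a·r, so the bias is −a·r. Take τ = 1.0, the standardised difference in Sample size. The values of a and r are assumptions.

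- a = 0: 1.0 − 0 = 1.00 (no bias)
- a = 0.3, r = 0.2: 1.0 − 0.06 = 0.94
- a = 0.5, r = 0.3: 1.0 − 0.15 = 0.85
- a = 0.8, r = 0.5: 1.0 − 0.40 = 0.60
- a = −0.3, r = 0.3: 1.0 + 0.09 = 1.09 (bias upwards)

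A simulation of 200,000 independent patients, total effect 1.0, separated the two routes. Satisfaction acted on outcome with slope b, and an unmeasured factor loaded u on both. The within-arm slope is then b + u², and the adjusted coefficient is 1 − a(b + u²):

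- a = 0.5, b = 0.5, u = 0.4: 1 − 0.5 × 0.66 = 0.67; simulated 0.67
- a = 0.5, b = 0, u = 0.4: 1 − 0.5 × 0.16 = 0.92; simulated 0.92
- a = 0.8, b = 0.5, u = 0.4: 1 − 0.8 × 0.66 = 0.47; simulated 0.47

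The second line shows bias even when satisfaction has no effect on outcome at all. Without satisfaction in the model, the estimate was 0.99 to 1.01 in every scenario.

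**3. Compliance, defined only in the intervention arm**

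- *Missing in controls.* A complete-case model keeps no control patient. Arm is then constant and its effect cannot be estimated. No assumption is needed here.
- *Coded 0 in controls.* The arm coefficient becomes the contrast at zero compliance. With 60% complying and an effect k of compliance (both assumed), it is 1 − 0.6k: 1.00 for k = 0; 0.82 for k = 0.3 (simulated 0.84, in a sample whose unadjusted estimate was 1.01); 0.64 for k = 0.6 (simulated 0.64).
- *Precision when coded 0.* With 30 independent patients per arm and outcome SD 1, the unadjusted SE is √(2/30) = 0.26. If compliance has mean 0.667 and SD 0.201 in the intervention arm (an assumed Beta(3, 1.5) distribution), the SE is √(2/30 + 0.667²/(29 × 0.201²)) = √(0.067 + 0.380) = 0.67.

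None of these figures allows for clustering by OP, so none is a forecast for the planned multilevel model.

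**The case against.** **A later exploratory model may be meant.** The section does announce a subsequent look at patient characteristics, and the confounder list is given as examples. That reading is possible. But the text names no such model, calls the variables confounders, and places them directly after the propensity-score adjustment for imbalance between arms. If an exploratory analysis was intended, it needs to be stated.

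**Satisfaction may not differ by arm.** All OPs receive the same three training sessions, and the arms differ by one psychiatric visit and the OP's follow-up of its plan. The shift could be nil, and then adjusting for satisfaction does no harm. This stands: the bias is conditional. A satisfaction rating taken before treatment would also escape the criticism, but its place among the process measures points the other way.

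**Compliance may be recorded in both arms.** The Abstract suggests so. If that is right, the choice between missing and zero in controls disappears, together with the figures in step 3. The variable remains post-randomisation, so the reasoning in step 2 still applies.

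**Three stronger readings go too far.** A reader might infer that the plan breaches intention to treat. Intention to treat means analysing patients as randomised; covariate choice changes what is estimated, and the principle is broken only if controls actually fall out of the model. A reader might also infer that the primary result is certain to be biased, or biased towards zero; the documents support neither. Finally, a reader might infer that fatigue and resilience are adjusted for at follow-up. The Analysis section does not say so, T0 measurements exist, and adjusting for the baseline value of an outcome is ordinary practice. Leaving out the time point is detail that an article commonly leaves to the full protocol.

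**Conclusion.** The point holds in conditional form. The protocol labels two process measures as confounders and enters them in the analysis without separating them from the intention-to-treat comparison. For compliance the fault follows from the document's own definitions: it arises after randomisation and, under Recruitment of patients and Secondary outcome measures, does not exist in controls. For satisfaction it rests on the process-measure label, since no time point is given.

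An arm effect adjusted for either variable is biased for the effect of offering consultation when two conditions hold: the arm shifts the variable, and the variable affects or shares causes with the outcome. The documents do not fix the size or the sign. Under assumed shifts of 0.3 to 0.8 SD and correlations of 0.2 to 0.5, the bias is −0.06 to −0.40 SD; it is zero with no shift and positive if the shift is negative. These are illustrations for independent patients.

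**What to change.** - Delete satisfaction and compliance from the covariates of the treatment-effect model, and state that they do not enter the propensity score.
- State that every covariate in that model, including fatigue and resilience, is the value measured at T0.
- Report satisfaction by arm. Report compliance descriptively within the intervention arm, or use it in a separately labelled exploratory analysis.
- Reconcile the Abstract with Secondary outcome measures on what compliance or adherence refers to and in which arms it is recorded.

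The cost is a sentence or two in the Analysis section and one wording correction. Data collection, sample size and patient care are unchanged.

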### Time-frame of the study

The preparatory period will be 6 months. Subsequent to the approval of the Medical Ethics Committee, the OPs will be recruited and the psychiatrists will be trained. The inclusion and intervention phase will take 12 months. The follow-up phase will be 12 months, and data-analyses will last for 6 months. The total duration of the study will be 3 years.

### Ethical principles

The study has been planned, and will be executed in accordance with the principles laid down in the Helsinki declaration (Edinburgh, Scotland amendment, October 2000). Participation in the study will be voluntary, and written informed consent will be obtained. Patients will be explicitly informed of the fact that they can withdraw their consent to participate at any time, without specification of reasons and with no negative consequences for their future medical treatment. Patients who wish to withdraw from the study will receive CAU. The study has been approved by the Medical Ethics Committee of the METiGG, Kamer Zuid protocol 5.127.

## Discussion

### Strengths and limitations

One limitation of the study might be that the organization of care in companies could be a hazard, because this sector is under pressure to work more and more efficiently. It might also be difficult to establish regular contact between OPs, consultant psychiatrists and GPs, because OPs generally work supraregionally. Specific attention will be paid to limitations in implementation due to regional differences.

A strength of the study might be that early consultation could be very helpful to enhance early RTW, and thus might also improve recovery from a mental disorder. By embedding the psychiatric consultation in the company care setting, timely access to specialist care will be improved and discontinuity of care will be avoided.
